
#### Objective 2: association between quantified microorganism load and pregnancy outcomes

We will investigate the hypothesis that the quantity of microorganisms with inflammatory potential is associated with gestational age at birth. For this, we will analyse the vaginal microbiota data jointly with sexually transmitted infections and *Candida* spp diagnostic test results during pregnancy (these will be considered as additional covariates in the above-mentioned regression models). We will develop a ‘vaginal inflammation index’ based on quantification of the vaginal microbiota and their inflammatory potential^49^ and of yeasts. This vaginal inflammation index will also be analysed as a fixed effect in mixed-effects models with pregnancy outcomes as the outcomes; these models will not include any of the infection parameters that were used to design the index.

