### Study procedures and visits

At the enrolment visit, study field workers administer a questionnaire to record sociodemographic, behavioural and clinical information in an online Research Electronic Data Capture (REDCap)^30^ software database. The study nurse examines the woman, according to the South African government standard of care.^31^ As an additional procedure, a study nurse with training in obstetric ultrasound performs an abdominal ultrasound to estimate the gestational age. If this is later than the eligibility criterion, the participant is excluded from any further study activity. A study nurse collects vaginal samples (figure 1) for on-site testing for *C. trachomatis* and *N. gonorrhoeae* using the Xpert CT/NG assay on the Gene Xpert platform (Cepheid, Sunnyvale, California, USA) and for further off-site laboratory testing (see ‘Specimen collection and analysis’).

If the test result for *C. trachomatis* or *N. gonorrhoeae* is positive, the woman receives immediate antibiotic treatment if still on-site or is contacted by telephone and asked to return to the clinic for treatment. Antibiotic treatments are first-line regimens according to South African guidelines: for *C. trachomatis*, 1 g oral azithromycin and for *N. gonorrhoeae*, 500 mg intramuscular ceftriaxone (250 mg until South African treatment guidelines for sexually transmitted infections changed in December 2022).^32^ Women with vaginal discharge syndrome but with negative Xpert test results for *C. trachomatis* and *N. gonorrhoeae* receive empirical treatment for trichomoniasis with metronidazole 400 mg twice a day for 7 days. The study nurse gives advice to women with *C. trachomatis* or *N. gonorrhoeae* on safe disclosure of her diagnosis to her partner(s) and gives her a notification slip(s) to request her partner(s) to attend a clinic for treatment.

A follow-up visit at 30–34 weeks (third trimester visit) is scheduled at which clinical and obstetric information, as well as the same vaginal specimens, is collected and treatment given, if indicated.

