#### Objective 1: association between specified exposures and pregnancy outcomes

We will examine a primary set of microorganisms as exposures, detected at either enrolment or at the third trimester visit: *M. genitalium, M. hominis*, *U. urealyticum, U. parvum, T. vaginalis* and *Candida* spp are the microorganisms for which women did not receive diagnostic tests and treatment during study visits. We will use the mean and SD for the continuous outcome (gestational age) and absolute and relative frequencies for the binary outcomes (all secondary outcomes). Gestational age at birth for each exposure will be compared using Student’s t-test and a mean difference with 95% CIs (continuous outcome) and Fisher’s exact test and a risk difference with 95% CIs (binary outcomes).To control for confounding, multivariable regression models will be fitted to all outcomes with a set of prespecified potential confounders (age, educational level, alcohol consumption, HIV infection, prior preterm birth) for all organisms. For analyses of *M. genitalium*, *T. vaginalis* and *Candida* spp, we will also control for bacterial vaginosis (Nugent score 7–10). The other genital mycoplasmas can be identified from 16S rRNA amplicon sequencing in women with vaginal dysbiosis, so are sometimes considered part of bacterial vaginosis. For these organisms, we will conduct descriptive analyses, stratified by the presence of bacterial vaginosis. For continuous confounders, a linear relationship will be assumed by default but transformations (eg, log) or more flexible approaches (eg, splines or fractional polynomials) will be considered if there is evidence for non-linearity. For the continuous outcome, we will use linear mixed-effects regression models (including data from either visit and the participant as random effect) and report the result as mean difference with 95% CIs. For the binary outcome, we will use logistic mixed-effects regression and report the result as ORs with 95% CIs.Comparisons for associations with timing of detection, other microorganism exposures and birth outcomes will be considered secondary analyses. Associations between vaginal microbiota composition and pregnancy outcomes will be assessed. We will use compositional multivariable analysis methods to identify bacterial taxa that are differentially abundant between binary pregnancy outcome groups at the level of individual taxon relative abundances. We will use mixed-effects models (with the individual participant as the random effect and including data from both visits) to assess associations between continuous and binary pregnancy outcome and the following fixed effects derived from the vaginal microbiota data: alpha diversity, vaginal microbiota types and absolute abundances of predefined bacterial groups.^46^ These models will be adjusted for confounding as described in the previous paragraph.

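### The microbiota models pool enrolment samples with third-trimester samples taken after study antibiotics, and the stated adjustment set has no treatment term; the bias can go in either direction.

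*Protocol article*

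**What the plan says.** **Treatment and sampling** (Protocol article, Study procedures and visits). Vaginal samples are taken at enrolment. If the Xpert test is positive for *C. trachomatis* or *N. gonorrhoeae*, "the woman receives immediate antibiotic treatment if still on-site or is contacted by telephone". Women with discharge syndrome and a negative Xpert result "receive empirical treatment for trichomoniasis with metronidazole 400 mg twice a day for 7 days". At 30–34 weeks clinical information, "as well as the same vaginal specimens, is collected and treatment given, if indicated".

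**Microbiota models** (Objective 1). For alpha diversity, microbiota types and absolute abundances: "We will use mixed-effects models (with the individual participant as the random effect and including data from both visits) to assess associations". On adjustment: "These models will be adjusted for confounding as described in the previous paragraph". The set referred to is "age, educational level, alcohol consumption, HIV infection, prior preterm birth".

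**Inflammation index** (Objective 2). "This vaginal inflammation index will also be analysed as a fixed effect in mixed-effects models with pregnancy outcomes as the outcomes". The section does not itself say which visits supply the index. It does say that infection and *Candida* results will be considered as further covariates in the regression models, and that index models leave out infection parameters from which the index was built.

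**The concern.** Enrolment is before 27 weeks and the second sample is at 30–34 weeks, so the samples are more than 30 − 27 = 3 weeks apart. The study gives antibacterials to a selected group after the first sample. In that group the second sample measures a microbiota that treatment may have changed.

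Treatment is not random. It follows a positive test or symptoms, which may themselves be related to gestational age at birth. It can therefore be linked both to the measured third-trimester value and to the outcome, and the stated adjustment set leaves it out.

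At stake is how the microbiota results, and possibly the index results, can be read. If treatment can push the slope either way, neither a null nor a positive finding from the pooled model is safe to interpret. Any comparison by timing of detection that uses microbiota values has the same problem at the second visit.

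**Working it through.** **1. Is there a figure in the plan to reproduce?** Not on this point. The only calculation is the Objective 1 sample size. With two-sided alpha 0.05/6, 80% power, a 1-week difference, SD 2 and 10% exposed, the two-group t-test formula gives 54 exposed and 540 women in total, and 550 women give 80.7% power. That agrees with the stated 500–600. It concerns presence of an organism in a univariable comparison and does not bear on treatment.

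**2. What marks treatment in the stated models?**

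| Treated group | In the five confounders? | Marked by infection results under Objective 2? |
|---|---|---|
| Xpert positive (azithromycin or ceftriaxone) | No | Partly |
| Discharge syndrome, Xpert negative (metronidazole) | No | No; the Xpert result is negative by definition |

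The proxy in the first row is partial for two reasons. A positive result is not receipt, since some women must be recalled by telephone. If results enter visit by visit, a woman treated and cleared is coded negative on exactly her post-treatment row.

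**3. Direction, by algebra.** Take the third-trimester value alone and suppose it drives the outcome:

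- Outcome Y = βX + δT + error, where T is treatment and δ is the difference in treated women for other reasons.
- X = U − dT, where U is the load without treatment (SD 1), d is the fall due to treatment, and m is the treated-minus-untreated difference in U.
- With share p treated, the slope omitting T is b = β + δ·C/V, where C = p(1 − p)(m − d) and V = 1 + p(1 − p)[(m − d)² − m²].

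The sign of the bias is the sign of δ(m − d). The documents give none of these quantities. Illustration, all inputs assumed: β = −0.3 week per SD, p = 0.2, δ = −0.5 week, m = 0.5 SD, so p(1 − p) = 0.16.

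| d | C | V | b | b/β |
|---|---|---|---|---|
| 1 (load lowered) | 0.16 × (−0.5) = −0.08 | 1.00 | −0.3 + 0.04 = −0.26 | 0.87 |
| 0.5 (load lowered) | 0 | 0.96 | −0.30 | 1.00 |
| −0.5 (load raised) | 0.16 × 1 = 0.16 | 1.12 | −0.3 − 0.071 = −0.371 | 1.24 |

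So the bias may be towards the null, absent or away from it.

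**4. Size in the pooled model, by simulation.** Assumed inputs: two visits per woman, load correlation 0.6, slope −0.3 week per SD, outcome SD 2, treatment likelier at higher enrolment load, 10–30% treated. The analysis was ordinary regression on both visits with a visit term. Ratio of the slope without a treatment term to the slope with nobody treated:

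| Treatment effect on load | Other difference in treated women | Ratio |
|---|---|---|
| Lowered 0.5 or 1 SD | none | 0.87–0.99 |
| Lowered 0.5 or 1 SD | +0.5 week | 0.74–0.92 |
| Lowered 0.5 SD | −0.5 to −1 week | 1.06–1.35 |
| Raised 0.5 SD | −0.5 to −1 week | 1.17–1.84 |
| Raised 0.5 SD | +0.5 week | down to 0.61 |

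For the third-trimester slope alone the range was about 0.45 to 1.8.

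**5. Which repair works under these assumptions?**

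- Pooled model with a single yes/no term for treatment before the sample: about 0.7 to 1.4, so not enough.
- Pooled model with treatment and treatment-by-visit terms: about 0.94 to 1.03.
- Third-trimester model with a treatment term: about 0.92 to 1.00.

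How complete the recovery is depends on how strongly treatment follows enrolment load, so these figures show that the repair helps and do not guarantee that it removes all bias.

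**The case against.** **The article is an overview and a detailed analysis plan is to follow.** This is the strongest objection and it limits the weight of the point. But the article does more than stay silent: it states a confounder set for these models, and that set omits a treatment the study itself gives.

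**Infection results are to be considered as covariates.** This stands in part. A reader might infer that nothing in the models relates to treatment, which goes too far. *C. trachomatis* and *N. gonorrhoeae* results are a proxy for one treated group. They are not named as index components, so they are not clearly barred from the index models. The metronidazole group remains unmarked.

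**Attenuation.** A reader might infer that antibiotics pull these associations towards the null. For example, take a high/low index split 50:50 with a true 1-week difference. If treatment moved 20% of truly high women to low, the low group would be 0.1/0.6 = 17% truly high and the third-trimester difference 0.83 week; moving 40% gives 0.2/0.7 = 29% and 0.71 week. These shares are assumptions, the sums concern the third trimester alone, and they cover only the attenuating case. The documents support no fixed direction.

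**If current load drives labour, the post-treatment value is the right exposure.** Correct, and then there is no misclassification. The confounding in step 3 remains, because that calculation assumes exactly this.

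**The stated model has a different route to zero.** Gestational age is one value per woman. Repeating it on two rows with a participant random intercept gave a slope of about 0 in simulated data on 550 women with nobody treated, against −0.22 by ordinary regression. That is a separate matter and no evidence of a treatment effect; it is why step 4 used ordinary regression.

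**Conclusion.** The point holds in a limited form. The protocol pools pre-treatment values with values that are post-treatment in a selected group of women, and the stated adjustment set has no term for that treatment. The microbiota associations may be biased in either direction.

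For the inflammation index the point is conditional. A reader might infer that it too is pooled over both visits, but Objective 2 does not say so; pooling is explicit only for the Objective 1 microbiota models.

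The size is unknown. The range of 0.61 to 1.84 rests wholly on assumed treated shares, treatment effects and risk differences. The introduction's figure of around 30% with a curable infection in pregnancy is background, not the treated share here. The analyses affected are outside the primary exposure set of Objective 1 or belong to Objective 2, and the separate analysis plan may already deal with this, so the change is advisable and does not threaten the study's main comparison.

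**What to change.** In Objective 1, and in Objective 2 wherever third-trimester values are used:

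1. Estimate the enrolment and third-trimester associations separately, or in one model with visit interactions.
2. For the third-trimester estimate, add receipt of any study antibiotic between the visits as a covariate. In a pooled model use treatment plus treatment-by-visit terms; a single pre-sample indicator is not sufficient. Define it from receipt, not from the test result, so that metronidazole for discharge syndrome is counted.
3. Report a sensitivity analysis in women not treated between visits.
4. State which visits supply the inflammation index.

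The cost is analysis-plan wording and one or two more parameters, provided that study records show receipt. The sensitivity analysis uses a smaller sample selected on infection and symptoms, so it should support the adjusted estimate and not replace it.

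Separately, Objective 1 places *T. vaginalis* among the organisms for which women were neither tested nor treated at study visits, while Study procedures and visits describes empirical trichomoniasis treatment for some women. These two statements must be reconciled.

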#### Objective 3: classification and regression tree analysis for the primary outcome

We will conduct exploratory analyses to examine the combination of microorganisms that best predicts earlier gestational age at birth using classification and regression tree analysis.^50^ This method belongs to the family of decision tree machine learning algorithms and allows for non-parametric analyses of a large number of binary, categorical or continuous predictors. They are typically easy to interpret and can detect predictors with small marginal effects when there are strong interaction effects. We will make use of the predictive potential for gestational age at birth of all sexually transmitted and genital tract microorganisms, including individual bacterial taxa or bacterial groups identified by 16S rRNA gene amplicon sequencing (as binary or continuous variables) and confounding variables identified in objective 1. We will present variable importance scores and curves of marginal effects to show how prediction of the outcome changes at different levels of the exposure of each variable in the model. To avoid overfitting, we will consider bootstrap aggregating via random forests.^51^

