#### Microbiological analyses

The Xpert vaginal swabs are tested on-site using the Xpert CT/NG assay (Cepheid) to detect *C. trachomatis* and *N. gonorrhoeae*, as per manufacturer’s instructions. At the University of Pretoria, air-dried vaginal smears are heat fixed and Gram stained.^36^ Two qualified people record the Nugent scores (0–3: normal; 4–6: intermediate; 7–10: bacterial vaginosis) and the presence of yeasts.^37^ In case of discrepancies, a third person assesses the slide and consensus is reached by discussion. At the University of Pretoria, one vaginal FLOQSwabs is used for PCRs. The genomic DNA is extracted using the High Pure PCR Template Preparation Kit (Roche Diagnostics, Mannheim, Germany) as per manufacturer’s instructions. Real-time PCR assays are then performed using the LightCycler 480 Probes Master Kit (Roche Diagnostics) on the LightCycler 480 II instrument (Roche Diagnostics). Previously published primer and hydrolysis probe sequences and cycling conditions are used for detection and quantification of *M. genitalium*,^38^
*M. hominis*,^39^
*U. parvum*,^40^
*U. urealyticum,*^40^
*T. vaginalis*^41^ and *Candida* spp.^42 43^ The load for each assayed microorganism detected in vaginal swab specimens by real-time PCR or GeneXpert is obtained from the cycle threshold value.

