### Sample size calculation

The sample size has been calculated for objective 1, with a univariable comparison between the presence of a genital tract microorganism in the mother and gestational age at birth. Figure 2 shows that, for any vaginal or sexually transmitted microorganism, or vaginal microbiota type that has a prevalence of 10% or more among all enrolled women, about 500–600 patients provide adequate power (80%) to detect a 1-week difference (with SD 2) in mean gestational age between the two groups using Student’s t-test. Specifying an alpha of 0.83% allows for multiple hypothesis testing (six hypotheses, using a Bonferroni correction). We enrol around 600 women and aim to have complete follow-up and outcome data on at least 550 women.

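### Objective 3 combines binary and continuous predictors in one CART model and promises importance scores, with no guard against the preference of exhaustive split search for variables with many cut points

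*Protocol article*

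**What the plan says.** The section on Objective 3 sets out the task: "We will conduct exploratory analyses to examine the combination of microorganisms that best predicts earlier gestational age at birth using classification and regression tree analysis". Among the merits of the method it lists that it "allows for non-parametric analyses of a large number of binary, categorical or continuous predictors". The candidate predictors are every organism the study tests for and, in the same model, these further variables: "individual bacterial taxa or bacterial groups identified by 16S rRNA gene amplicon sequencing (as binary or continuous variables) and confounding variables identified in objective 1". The promised output is stated firmly: "We will present variable importance scores and curves of marginal effects". The only safeguard is conditional and has another purpose: "To avoid overfitting, we will consider bootstrap aggregating via random forests".

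The section names neither a split rule nor a type of importance score, and it does not say how the PCR and Xpert organisms will be coded. Continuous values exist for them, because under Microbiological analyses "The load for each assayed microorganism detected in vaginal swab specimens by real-time PCR or GeneXpert is obtained from the cycle threshold value". The Statistical analysis section describes itself as an overview and promises a separate detailed analysis plan.

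**The concern.** At each node, standard CART searches every cut point of every variable and keeps the split that most reduces squared error. A present/absent organism offers one cut point. A taxon abundance measured in 550 women offers hundreds. Even if neither is related to gestational age, the taxon's best gain is a maximum over many looks and the organism's gain is a single draw. The contest therefore rewards the number of cut points as well as the association. Importance scores built from split gains inherit this, in a single tree and in a random forest.

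At stake is the ranking that Objective 3 is meant to produce: which organisms, in which combinations, best predict earlier birth. The Discussion says the study will generate hypotheses for later work. A ranking that partly reflects how finely each variable was measured would point that work in the wrong direction.

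**Working it through.** **1. Inputs from the protocol.** Under Sample size calculation the study is sized "to detect a 1-week difference (with SD 2) in mean gestational age between the two groups using Student’s t-test", for an exposure that "has a prevalence of 10% or more among all enrolled women". Power is 80%, alpha is 0.83% and at least 550 women should have complete data. Objective 3 gives no figure of its own.

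**2. Reproducing the plan's figure.** Taking alpha as two-sided, N = (z₁₋α/₂ + z₀.₈)² σ² / [p(1−p)d²]. With z = 2.640 and 0.842, this is 12.12 × 4 / 0.09 = 539. The exact t-test gives 543, and power at 550 is 0.807. The stated 500–600 is confirmed, so the effect used below is the one the study was designed to detect.

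**3. The gain.** A split into groups of size n_L and n_R has gain G = (n_L n_R / N)(ȳ_L − ȳ_R)². For a binary organism, the expected value of G/σ² is about 1 + N p(1−p) d²/σ²:
- 10% prevalence, 1 week: 1 + 550 × 0.09 / 4 = 13.4
- 10% prevalence, 0.5 week: 1 + 550 × 0.09 × 0.25 / 4 = 4.1
- 30% prevalence, 1 week: 1 + 550 × 0.21 / 4 = 29.9

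A null continuous taxon scores the maximum of up to 537 correlated draws (left-hand group sizes 7 to 543 with a minimum leaf of 7), each with expectation about 1. Only the ordering of its values matters, so its distribution is irrelevant apart from ties.

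**4. First split, by simulation** (N = 550, SD 2, minimum leaf 7, independent null competitors; 20 is an assumed number). With no effect anywhere, one null continuous taxon beats one null binary organism in about 94–95% of runs; 50% would be fair. With a true organism effect, the best of 20 null competitors wins as follows. Ranges span repeated simulations, the largest with 1,500 runs per cell.

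| Prevalence | Effect (weeks) | 20 continuous taxa | 20 binary competitors |
|---|---|---|---|
| 10% | 0.5 | 90–95% | 63–65% |
| 10% | 0.75 | 76–77% | 34–38% |
| 10% | 1 | 40–46% | 10–13% |
| 30% | 0.5 | 73–74% | 30–34% |
| 30% | 0.75 | 25–27% | 5–6% |
| 30% | 1 | 1–4% | about 0% |

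The last column is the cost of having 20 competitors at all. The gap between the two columns is the share due to cut points. At 10% prevalence, one given null taxon wins in about 65% of runs at 0.5 week and 12–14% at 1 week. Zero-inflated taxa (50–80% zeros) reduce the bias without removing it: at 10% prevalence the best of 20 still wins in 86–93% at 0.5 week and 26–38% at 1 week.

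**5. Importance scores** (10% prevalence, 20 null continuous taxa; 25–30 runs per cell, so approximate). The entries are the mean number of null taxa ranked above the real organism.

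| Score | 0.5 week | 1 week |
|---|---|---|
| Single tree, split gain | 11 | 6 |
| Forest, split gain | 20 | 18–19 |
| Forest, permutation on independent data | 7–8 | 1.2–1.5 |

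With permutation importance at 1 week, the organism ranked first in about 63% of runs. A separate simulation with 8 binary organisms and 30 continuous taxa (assumed numbers) used out-of-bag permutation. The median rank of the truly associated organism was 31 of 38 by split gain and 3 of 38 by permutation.

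**6. Does unbiased split selection help?** In that 38-variable setting, at 1 week and 10% prevalence, CART split on the true organism first in 47% of runs. Choosing the variable by its association p-value, the principle behind conditional inference trees, did so in 79%. With taxa 60% zeros the figures were 63% and 86%; with 10 such taxa, 76% and 89%.

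**7. Does coding organisms by load cure it?** Only partly. With the organism coded as load (10% positive, the rest zero) and no effect, it beats one null continuous taxon in 21% of runs, against 5% when binary. With a 1-week effect that depends on presence alone and 30 null taxa, it takes the first split in 57%, against 50% when binary. With taxa 60% zeros this is 66% against 60%. An organism absent in 90% of women still has few distinct values.

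**The case against.** The strongest reply is that the article does not fix the choices that produce the bias. It names no split rule or importance score, leaves the coding open and supplies organism loads, so every predictor could be continuous or every one binary. A separate analysis plan is promised and may settle these points. The objective is labelled exploratory, and the six primary organisms are tested on their own under Objective 1, for which the study is sized. The number of taxa is assumed, and bacterial groups could be few. The simulations use one main effect and mostly the first split, whereas trees are justified here by interactions; missing the first split does not mean being absent from the tree.

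Much of this stands, and it limits the size and certainty of the point. It does not remove it. The section goes beyond silence: it names the method, admits mixed predictor types to one model and presents that as a merit, and commits to importance scores. The one safeguard it mentions is optional and aimed at overfitting, and if forest importance is scored by split gain the ranking becomes worse. An analysis plan that followed the section to the letter could inherit the bias.

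A reader might infer that real organism effects will rank behind null taxa whatever the truth, or that Objective 3 is designed to set infections against microbiota. The documents support neither. Coding and score are open, the loss nearly vanishes at 30% prevalence and 1 week, and no section gives Objective 3 that adjudicating role.

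**Conclusion.** The concern holds as a tendency, conditional on coding. Where organisms enter as present/absent, or as load with mostly zero values, and taxa enter as continuous, CART split choice and split-gain importance favour the taxa. At the design effect and the lowest design prevalence, with an assumed 20 null taxa, the first split goes to a null taxon in about 40–46% of runs, of which 10–13 points would arise from 20 binary competitors anyway. The problem is larger for smaller effects and small for common organisms with a 1-week effect. In a forest, the type of importance score decides the matter: split gain misranks the organism almost always in these settings, while permutation largely does not.

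The figures rest on independent taxa, assumed numbers of taxa, a single main effect, and few runs for the forests. Because the objective is exploratory, the primary analysis is untouched. The change is worth making because it improves the ranking at almost no cost; the plan is not invalid without it.

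**What to change.** In the Objective 3 section, and in the detailed analysis plan, state that:
- variable importance will be permutation-based (out-of-bag), not split-gain;
- trees will use unbiased split selection, through conditional inference trees or forests, at least alongside CART. Dropping CART altogether is not essential.

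It would also help to state how the PCR and Xpert organisms and the 16S taxa are coded. Putting all predictors on a common scale is only a partial remedy unless all are dichotomised.

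The cost is a different software routine and a sentence or two, with no new data. The downside is somewhat longer computing time and usually smaller trees.
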